The clinical study presented here focuses on the second point and aims to evaluate the efficacy of coenzyme Q10 in a specific subgroup of PD patients. Several clinical trials with coenzyme Q10 in PD patients have already been performed. Published results on the efficacy of coenzyme Q10 given to unselected PD patients are heterogeneous arguing that a global efficacy for all PD patients seems questionable [2, 8]. Coenzyme Q10 has antioxidant properties, which could mediate global efficacy, and additionally acts as a mitochondrial electron transporter, which can mediate improvement in mitochondrial function [10]. Disturbances of mitochondrial function have been proven for hereditary PD caused by mutations in the genes *Parkin* and *PINK1* [5]. The central hypothesis of this study is that coenzyme Q10 is particularly effective for PD patients with expected mitochondrial dysfunction. For this purpose, PD patients will be stratified based on their genetically determined expected mitochondrial dysfunction.

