### Outcome measures

The primary endpoint of the study is the change severity of PD motor symptoms after six months of treatment. The primary endpoint is measured as the difference between Part III of the revised version of the Unified Parkinson’s Disease Rating Scale (MDS-UPDRS) six months after randomization and baseline measurement. The minimally clinically relevant difference of the UPDRS III score in PD patients has been investigated in many studies providing heterogeneous results. The type I-error is set to 5% (two-sided). No previous study has taken the genetic status of PD patients into account when investigating the efficacy of coenzyme Q10. The parameters used for the power analysis are based on the work of Shulman et al. [7]. If the clinically relevant difference in the UPDRS Part III in the P++ group is large (mean = 38, standard deviation (SD) = 13.4) and there is no difference in the omics- group (mean = 27.2, SD = 13.4), while the P+ group and the omics+ group have intermediate values (mean = 34.4 and 30.8 with both SD = 13.4, respectively, the power to detect a negative slope of the interaction in the linear regression is 56% if 12, 12, 24, and 24 patients are randomized 1:1 within the four genetic groups P++, P+, omics+, and omics-. If the effect size is 1, which corresponds to a linear trend and a mean UPDRS III of 40.6 in the P++ group, the power of the study increases to 76%. We do not expect any study-related loss of patients (lost to follow-up) for the monogenetic groups (P++ and P+), as these patients have been in regular contact with the trial centers for several years. For the two omics groups, we expect patients lost to follow-up of 5%. This was the median in the four randomized clinical trials of coenzyme Q10 in PD patients conducted to date [4]. The work of Goetz et al. [3] compares the MDS-UPDRS with the original UPDRS and reports a high correlation between scales, especially for the motor part III (r = 0.96, R2 = 0.92). The case number determined for the UPDRS Part III is therefore adjusted by the factor 1/R2, resulting in a case number of approximately eighty-four patients, with approximately fourteen patients each in the two monogenic groups and approximately twenty-eight patients each in the two omics groups. Secondary clinical endpoints include quality of life (Parkinson’s Disease Quality of Life Questionnaire [PDQ39]), depression (Beck’s Depression Inventory II, BDI II), motor fluctuations and disease-related complications (MDS-UPDRS IV), daily activities (MDS-UPDRS II), fatigue (Fatigue Severity Scale [FSS]), sleepiness (Epworth’s Sleepiness Scale [ESS] and Parkinson’s Disease Sleep Scale 2 [PDSS2]), and cognitive function (Montreal Cognitive Assessment [MoCA]) (see Table 1). Secondary endpoints also include magnetic resonance imaging of brain energy metabolism (31P-magnetic resonance spectroscopy imaging [MRSI], see Fig. 3), as well as changes in structural, and functional brain anatomy (MRI). The secondary efficacy endpoints are evaluated in an explorative manner analogous to the primary endpoint. All relevant safety endpoints are described descriptively with suitable statistical measures.

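### The stated 56% and 76% power for the treatment-by-genetic-group slope does not follow from the printed inputs, which give about 22% and 32%

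*Protocol article*

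**What the plan says.** Under Study description and study design, the protocol article sets the primary hypothesis as a treatment effect that changes linearly over the ordered groups omics-, omics+, P+ and P++. Under Outcome measures it powers that hypothesis:

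- Error rate: "The type I-error is set to 5% (two-sided").
- P++: the relevant difference "is large (mean = 38, standard deviation (SD) = 13.4").
- Omics-: "there is no difference in the omics- group (mean = 27.2, SD = 13.4").
- P+ and omics+: "intermediate values (mean = 34.4 and 30.8 with both SD = 13.4, respectively").
- Result: "the power to detect a negative slope of the interaction in the linear regression is 56% if 12, 12, 24, and 24 patients" are randomised 1:1 within P++, P+, omics+ and omics-.
- Larger effect: "If the effect size is 1, which corresponds to a linear trend and a mean UPDRS III of 40.6 in the P++ group", then "the power of the study increases to 76" per cent.

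The endpoint is the six-month change in MDS-UPDRS Part III. The article prints no SD of change and no correlation between baseline and six months, and it does not list the terms of the regression. The target of 72 is later raised to about 84 (14/14/28/28) to allow for the change of rating scale.

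**The concern.** The primary test concerns a difference between treatment differences. Each monogenic group supplies only 6 patients per arm, and the assumed step between neighbouring groups (3.6 points) is about a quarter of the SD (3.6/13.4 = 0.27). Power of 56% looks high for that contrast.

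If the printed inputs are right, the trial would miss the large assumed effect about 78% of the time, not 44%. A reader who weighs a non-significant slope against a power of 56% or 76% would give it more weight than the design supports.

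**Working it through.** **Inputs** (all from Outcome measures)

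- Two-sided 5%; SD 13.4 in every group.
- Omics- has no effect, so 27.2 is the reference mean. The treatment differences are 38 − 27.2 = 10.8, 34.4 − 27.2 = 7.2, 30.8 − 27.2 = 3.6 and 0, which is a slope of 3.6 per group step.
- Larger effect: 40.6 − 27.2 = 13.4, which is 1 SD. The slope is 13.4/3 = 4.467 per step.
- 12/12/24/24 patients, so 6/6/12/12 per arm.
- Group score S = 3, 2, 1, 0 for P++, P+, omics+, omics-. Equal spacing matches the equal steps in the printed means.

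**Attempt to reproduce 56% and 76% with an interaction model**

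Model: Y = b0 + b1·T + b2·S + b3·T·S, with T = 0 or 1. The slope of the interaction is b3.

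- Sum of S = 12·3 + 12·2 + 24·1 = 84. Sum of S² = 12·9 + 12·4 + 24·1 = 180.
- Sxx = 180 − 84²/72 = 82 overall, so 41 per arm.
- SE(b3) = 13.4·√(1/41 + 1/41) = 13.4·√(2/41) = 2.96.
- Noncentrality: 3.6/2.96 = 1.216 and 4.467/2.96 = 1.509.
- Noncentral t, 68 df: power 22.4% and 31.9%. Simulation gives 22.3% and 32.0%.

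The stated figures are not reproduced. Other readings of the same text, with SD 13.4:

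| Reading | Power, P++ mean 38 | Power, P++ mean 40.6 |
|---|---|---|
| Stated in the article | 56% | 76% |
| Treatment, score and product, N = 72 | 22% | 32% |
| Same, one-sided 5% | 33% | 44% |
| Same, final N = 84 | 25% | 36% |
| Same, 12/12/24/24 per arm (N = 144) | 40% | 56% |
| Treatment main effect omitted | 43% | 60% |
| Group main effect omitted | 40% | 56% |
| Both main effects omitted | 57% | 76% |

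**What does reach the stated pair**

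1. *A smaller residual SD with the full model.* At SD 7.6, SE = 7.6·√(2/41) = 1.68 and power is 56.1% and 74.6%. At SD 7.5 it is 57.2% and 75.7%. For a change score, SD of change = 13.4·√(2(1 − r)). With r = 0.84 this is 7.58, and power is 56.4% and 74.9%. The correlation is an assumption; the article prints none.

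2. *A regression on the product T·S alone.* The sum of T·S is 42 and its sum of squares is 90, so Sxx = 90 − 42²/72 = 65.5. Then SE = 13.4/√65.5 = 1.656 and power is 57.3% and 75.8% (70 df).

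Route 2 would not isolate an interaction. In simulation with 72 patients, SD 13.4, a uniform treatment effect and no interaction, its nominal 5% test rejects in about 16% of trials for a 5.2-point effect (an illustrative value) and about 50% for a 10.8-point effect. The full model stays near 5% in both cases.

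**Sensitivity to the unstated correlation** (full model, N = 72)

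| Assumed r | Change score | Adjusted for baseline, SD 13.4·√(1 − r²) |
|---|---|---|
| 0.5 | 22% / 32% | 28% / 40% |
| 0.7 | 34% / 48% | 39% / 55% |
| 0.8 | 47% / 65% | 52% / 70% |
| 0.84 | 56% / 75% | 60% / 78% |

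**The case against.** The strongest reply is that SD 13.4 accompanies means of 27.2 to 38, which look like score levels, while the endpoint is a change from baseline. If baseline and six-month scores correlate strongly, the residual SD is smaller and the stated power could be right for a proper interaction model. This stands as a possibility: the stated pair is met near r = 0.84 for a change score, and is passed between 0.80 and 0.84 with baseline adjustment. It does not rescue the paragraph as printed, because 13.4 is the only SD given and no correlation is mentioned.

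A reader might infer from the close match of the product-only regression that the main effects were left out, and that the primary test will therefore not hold its 5% level for effect modification. The Background does allow for a uniform effect: "Coenzyme Q10 has antioxidant properties, which could mediate global efficacy". But the documents do not support that inference. A residual SD of about 7.5 fits the stated pair equally well, and the wording of both the hypothesis and the power statement suits a standard interaction model. Listing the model terms is also something that an article may leave to the full protocol or analysis plan. The rejection rates of 16% and 50% are therefore hypothetical.

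The article also openly reports a power of only 56% for its main scenario and calls the study Phase II and proof of principle. Nowhere does it say that a null slope would refute the genetic hypothesis. That limits how far a misreading can be predicted, but not the numerical mismatch.

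**Conclusion.** The stated power contradicts the inputs printed beside it. At SD 13.4 and 72 patients, the treatment-by-group slope has about 22% power where 56% is stated, and about 32% where 76% is stated, so the stated figures are roughly 2.5 and 2.4 times too high. One-sided testing, the final 84 patients and per-arm counts do not close the gap.

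The result rests on equally spaced group scores, 13.4 as the residual SD of the analysed outcome, and a model with both main effects. It does not show that the trial's true power is 22%, since the SD of the change score is unknown. Nor does it show how the authors obtained their figures. It does show that 56% and 76% depend on an assumption that the article leaves out. Because this concerns the only primary test, it should be corrected.

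**What to change.** Compute the power from the regression that the primary hypothesis requires: treatment, group score and their product. Then do one of two things:

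- restate it as about 22% (P++ difference 10.8) and 32% (P++ difference 13.4) at SD 13.4 and 72 evaluable patients; or
- state and justify the SD of change, or the baseline correlation, at which 56% and 76% hold.

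This changes the wording of the power paragraph only. The first option makes the stated figure less favourable. Neither option needs more patients.

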### Study description and study design

The presented study is a multicenter, double-blind, controlled and randomized Phase II study in parallel group design, investigating the treatment of PD with coenzyme Q10 (156 mg/d QuinoMit® Q10 Fluid from MSE Pharmazeutika) in addition to best medical treatment compared to placebo. In each participating study center, potential study participants are examined for their genetic profile before inclusion in the study and assigned to one of the four genetic groups depending on their profile (see Fig. 1). Within the genetic groups, randomization to the experimental group or placebo control group is performed at a ratio of 1:1. The study duration per patient will be six months plus a three-month follow-up period (see Fig. 2). The primary endpoint is evaluated according to the Intention-to-treat (ITT) principle. This is practically implemented with the Full Analysis (FA) dataset (ICH E9, 1998), i.e., all registered patients who are included in the study and randomized are included in the analysis in the treatment group to which they were randomized. For the evaluation of safety, all registered and randomized patients who have received the investigational product (QuinoMit® Fluid or placebo) at least once are considered. The Per Protocol (PP) population is investigated in secondary analyses (sensitivity analyses). In the placebo group, this population consists of patients who have taken at least 80% of the investigational product. In the study group, the PP population consists of patients who took at least 80% of the investigational product and additionally had a coenzyme Q10 plasma level of at least 2.5 μg/ml at follow-up times three months and six months after randomization. The primary hypothesis of the study is that the motor symptoms of patients receiving coenzyme Q10 (QuinoMit Q10® Fluid) differ from those receiving placebo in the form of a linear difference in effect between omics-, omics+, P+, and P++.

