The number of effect alleles (coding 0 = no effect allele, 1 = one effect allele and 2 = two effect alleles) and the weighting of the respective SNP with the effect size of the effect allele, measured with the ln of the odds ratio, are incorporated into this score from each risk SNP. If the calculated risk score for a patient exceeds a threshold value of + 0.30, this patient is assigned to the omics+ group. If a patient has a risk score of less than − 0.30, an assignment to omics- is made. Patients with a risk score between − 0.30 and + 0.30 do not belong to one of the two “extreme” omics groups. These patients are not included in the study if they are not heterozygous, homozygous or compound heterozygous for mutations in the *Parkin* or *PINK1* gene. In patients who are assigned to one of the two omics groups, mutations in the *PINK1* or *Parkin* gene will be excluded. The thresholds as mentioned above were determined to represent the 20 and 80% quantiles in our cohorts in which the score has been established. A number of the study participants’ samples will be genotyped twice in order to ensure the reproducibility of genotyping. In this way, the agreement can be determined SNP-specifically and overall. The intra-class correlation coefficient is used as a measure of agreement. It is suspected that the four groups differ in the degree of mitochondrial dysfunction, with increasing dysfunction from omics- via omics+ and P+ to P++. Accordingly, it is assumed that the efficacy of coenzyme Q10 treatment increases from omics- to P++. The aim is therefore to investigate the efficacy of Q10 as a function of genetic background. For each genetic subgroup, all secondary endpoints are analyzed exploratively.

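### The primary interaction regression is stated without treatment or genetic-group main effects, and at the only SD given (13.4) the published power fits a model that has neither

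*Protocol article*

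**What the plan says.** Under Study description and study design, genetic group is the randomisation stratum: "Within the genetic groups, randomization to the experimental group or placebo control group is performed at a ratio of 1:1". The same section states the primary hypothesis as a difference between CoQ10 and placebo "in the form of a linear difference in effect between omics-, omics+, P+, and P"++. So the target is a treatment-by-group gradient.

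Under Outcome measures, the endpoint is MDS-UPDRS III at six months minus baseline, and "The type I-error is set to 5% (two-sided"). The model appears only in the power statement: "the power to detect a negative slope of the interaction in the linear regression is 56" per cent with 12, 12, 24 and 24 patients in P++, P+, omics+ and omics-, and 76% if the P++ mean is 40.6. The other terms of the regression are not listed. The secondary efficacy endpoints are to be analysed in the same way as the primary, exploratively.

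Under Genetic stratification: "It is suspected that the four groups differ in the degree of mitochondrial dysfunction", increasing from omics- to P++.

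**The concern.** A product coefficient measures an interaction only when its component main effects are also in the model. Without a group term, any difference in six-month change between the genetic groups that is common to both arms is partly attributed to the product. Without a treatment term, so is a benefit that is equal in all groups. Either would look like the trial's central claim, that the effect of CoQ10 rises with mitochondrial burden.

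The groups differ in aetiology by design, so equal natural change in all four cannot be taken for granted. An article may leave model terms to the full protocol or analysis plan. Here, however, it prints two power figures, and these give some indication of which model was in mind.

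**Working it through.** **Inputs (Outcome measures).** omics-: "there is no difference in the omics- group (mean = 27.2, SD = 13.4"). Omics+ and P+: 30.8 and 34.4 ("mean = 34.4 and 30.8 with both SD = 13.4"). P++: "mean = 38, standard deviation (SD) = 13.4". Differences from 27.2 are 0, 3.6, 7.2 and 10.8, so the slope is 3.6 per group step. Second scenario: effect size 1 in P++, so 13.4/3 = 4.467 per step. Sizes omics-/omics+/P+/P++ = 24/24/12/12, split 1:1; two-sided 5%. Assumed: scores s = 0, 1, 2, 3, treatment T = 0/1, residual SD 13.4 (the only SD given).

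**Step 1. The plan's figures from the product-only model.** Let z = T x s. Treated patients number 12, 12, 6 and 6 at scores 0 to 3; all placebo patients have z = 0.
- Sum z = 12 + 12 + 18 = 42; sum z² = 12 + 24 + 54 = 90; Szz = 90 − 42²/72 = 65.5.
- SE = 13.4/√65.5 = 1.656.
- Noncentrality 3.6/1.656 = 2.17 and 4.467/1.656 = 2.70; noncentral-t power (70 df) **57.3% and 75.8%**. Stated: 56% and 76%.

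**Step 2. Main effects added.** With treatment and group in the model, the coefficient is the difference between two within-arm slopes. Each arm has sum of squares 90 − 42²/36 = 41.
- SE = 13.4 x √(2/41) = 2.960.
- Noncentrality 1.22 and 1.51; power **22.4% and 31.9%**, whether group is a linear score or a factor.

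| Model (N = 72, SD 13.4, two-sided) | Slope 3.6 | Slope 4.467 |
|---|---|---|
| Stated | 56% | 76% |
| Product only | 57.3% | 75.8% |
| + treatment | 39.6% | 55.8% |
| + group factor | 42.7% | 59.6% |
| + treatment and group | 22.4% | 31.9% |

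One-sided, the model with group but no treatment term gives 56% and 72%, which meets the first figure and misses the second. At the planned 84 patients (28/28/14/14), the full model has SE 13.4 x √(2/47.83) = 2.74 and power about 25% and 36%.

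**Step 3. What loads onto the product-only slope.**
- Natural gradient of g points per step, equal in both arms: Szs = 90 − 42 x 84/72 = 41, so the false slope is (41/65.5)g = 0.63g.
- Uniform treatment effect d: SzT = 42 − 42 x 36/72 = 21, so the false slope is (21/65.5)d = 0.32d.

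The ratios are the same at 28/28/14/14. Simulated rejection rates there, with SD 13.4 and no true gradient in the CoQ10 effect:

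| Assumed truth | Product only | Treatment + group factor + product |
|---|---|---|
| g = 1.34 (0.1 SD) per step | about 8% | 5% |
| g = 2.68 (0.2 SD) per step | 18% | 5% |
| Uniform 4-point benefit | 13% | 5% |

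**Step 4. Group as linear score or as factor, both main effects present.** With assumed non-linear group differences of ±0.3 or ±0.5 SD, a linear score raises the mean simulated SE from 2.73 to 2.79 or 2.88. Power at 3.6 per step falls from about 26% to 24% or 22%, and type I error to 4.4% or 4.0%. If the groups do not differ, the SE is the same either way.

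**The case against.** The strongest reply is that no sentence states a wrong model. The word interaction ordinarily implies its main effects, the article is a condensation, and a power calculation may be simplified without fixing the analysis. This stands in part: that the analysis omits main effects is an inference.

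The power figures also do not identify the model uniquely. The SD of 13.4 is attached to mean scores, while the endpoint is change. A full model with residual SD about 7.5 gives 57% and 76% at N = 72; that needs a baseline correlation of about 0.83 to 0.84. This is correct, but the article gives neither an SD of change nor a correlation. A smaller SD would also make the product-only bias worse: at SD 8, gradients of 1.34 and 2.68 points per step give about 15% and 44% false positives.

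The assumed gradients are not in the article either. At 2.68 per step, P++ and omics- would differ by 3 x 2.68 = 8.0 points in natural six-month change. The suspicion under Genetic stratification concerns the degree of dysfunction, not the rate of change. The false-positive rates are therefore illustrations.

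A reader might infer that the primary regression ignores genetic group. The article does not support that: the hypothesis and the slope are defined across the four groups. What is absent is a stated main effect for group and for treatment.

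**Conclusion.** The point holds in conditional form. The article states no main effects for its primary interaction test. Of the models tried at SD 13.4 with its own sizes and means, only one whose coefficient is not an interaction comes close to both power figures. If that model is the analysis, the two-sided 5% level is not protected, by the amounts in step 3. If main effects are intended, the level is safe but the published power is unsupported at the stated SD: 22% and 32% against 56% and 76%. Either way the specification needs correcting. The choice between a factor and a linear group score is a minor gain. The essential step is to include both main effects.

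**What to change.** State the primary model as: six-month change in MDS-UPDRS III regressed on treatment, genetic group as a four-level factor (the randomisation strata), and treatment x linear group score; the last coefficient is the primary test. Use the same terms in the analogous secondary analyses.

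This needs no new data. Compared with the product-only model it adds four parameters (one for treatment, three for group), so residual degrees of freedom at N = 84 fall from 82 to 78. Compared with a linear group score it costs two.

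The real cost is in power. At SD 13.4 this model has about 22% and 32% at N = 72, or about 25% and 36% at N = 84. Regaining 56% and 76% in the respective scenarios would take about 228 patients. The 56% and 76% must therefore be restated for this model, or a residual SD of about 7.5 (at N = 72) must be given and justified by an SD of change or a baseline correlation.

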**Fig. 3 Fig3:**
[figure not shown]
31P-Magnetic resonance spectroscopy imaging for the assessment of in vivo mitochondrial bioenergetics. 31P-MRSI spectra of a representative subset of brain parenchyma will be taken using a double-tuned P-headcoil (Advanced Imaging Research, Cleveland, Ohio). To attain sufficient relaxation of the phosphorus metabolites, a repetition time of 4500 ms will be used together with a three-dimensional chemical shift imaging sequence (6 × 5 × 3 voxel, 6 kHz bandwidth, 1024 data points, 8:51 min measuring time). The analysis procedures will follow an updated version of an already published protocol with an optimization of data acquisition. Peak positions and intensities will be calculated with the AMARES algorithm. We will examine adenosine triphosphate (ATP) and phosphocreatine (PCr), which reflects the overall high-energy phosphate turnover. PCr represents a high-energy reservoir linked to ATP in a bidirectional reaction in which ATP is formed by PCr and vice versa. In addition to PCr and ATP, the ratios of PCr/inorganic phosphate (iP) and ATP/Pi will be evaluated as an indicator of intracellular energy status within the scope of this study. A: 31P-MRSI spectrum. B: model fit on 31P-MRSI spectrum. C: background noise

